# Is transanal irrigation the best treatment possibility for low anterior resection syndrome? A multicenter, randomized clinical trial: study protocol

**DOI:** 10.3389/fsurg.2024.1384815

**Published:** 2024-05-13

**Keywords:** fecal incontinence, treatment of bowel dysfunction, colorectal surgery, low anterior resection syndrome, quality of life, transanal irrigation

## Abstract

**Background:**

Up to 50% of patients who undergo rectal resection suffer from various and partly severe functional problems, despite the preservation of the anal sphincter. These complaints are defined as low anterior resection syndrome (LARS). So far, there are no randomized clinical trials regarding the most effective treatment for LARS. Our aim is to evaluate whether transanal irrigation improves bowel function and quality of life in patients following low anterior resection compared to best supportive care.

**Methods:**

Patients who have undergone low anterior resection will be approached for this study. On patient's visit, complaints regarding the defecation as well as any deterioration in their overall quality of life will be assessed using questionnaires such as the Low Anterior Resection Syndromes score, Wexner score, European Organization for Research and Treatment of Cancer (EORTC) Quality of Life (QOL) CR-29, and Measure Yourself Medical Outcome Profile tool. Few additional target questions will be also asked, such as “Would you recommend the treatment to anybody; did you expect the improvement following the treatment; etc.” Questionnaires and scales will be filled on follow-up visits every 3 months for 1 year.

**Discussion:**

This multicenter, randomized controlled trial will lead to a better understanding of LARS treatment. Moreover, it will be a hypothesis-generating study and will inform areas needing future prospective studies.

**Clinical Trial Registration:**

ClinicalTrials.gov, identifier (NCT05920681).

## Introduction

Neoadjuvant treatment with low anterior resection and the formation of anastomosis provides excellent oncological results and is currently the gold standard of rectal cancer treatment (1). Preoperative chemoradiotherapy, vascular dissection, and surgical removal of the rectum and mesorectum cause significant colorectal motility impairment. This results in a variety of symptoms (multiple bowel movements, recurrent urge episodes, hoarding, urinary, fecal incontinence, etc.) that are associated with severe impairment of quality of life. These complaints are summarized as low anterior resection syndrome (LARS) (2). Moreover, surgery may lead to increased morbidity, prolonged hospital stay, readmission, sepsis, and death (3, 4).

Our previous studies showed the prevalence of LARS following rectal surgery in Lithuania reaches up to 75% (5). More importantly, it is a long-term effect—50% of patients have these symptoms 5 or more years after the surgery (6).

Transanal irrigation (enema) (TAI) is a promising treatment modality for LARS patients with increasing prospective data from published studies (7). Only a few clinical trials have been published in the literature where the benefit of transanal irrigations in the treatment of LARS has been investigated (8–10). In 2018, a study conducted in Italy (8), with 27 patients, evaluated transanal irrigation as a potentially beneficial treatment modality in the treatment of LARS. It was shown that the use of TAI demonstrates notable efficacy in treating LARS and resulted in improved continence and quality of life. However, this study included patients with chronic LARS as well as patients with early symptoms following the surgery. Some patients’ symptoms may improve over the time following the operation, while others can suffer from colonic dysfunction and nerve damage, which are strongly related to the main symptoms of LARS, but do not seem to be influenced by time (8). Similar studies were conducted in Germany (2018 and 2023) (9, 10), which have also shown the benefit of transanal irrigation in controlling LARS, but due to time constraints, some patients refused this method. While patients treated by TAI showed significant improvements in bowel movements, a notable portion decided to stop the treatment and relied on supportive therapy only (9).

Despite these data, the use of TAI remains a matter of debate. In addition, there are only few randomized clinical trials so far comparing TAI with best supportive care (8, 9, 11, 12). Main limitations of this study are that a significant amount of patients (six patients, reduction of 27.27%) dropped out of the intervention (TAI) group (9), the small numbers, and the short follow-up period (8, 11, 12).

Thus far, there are no randomized clinical trials confirming or denying the hypothesis regarding the most effective treatment for LARS. Treatment recommendations for LARS have been published in 2021 (13). Here, authors propose to initiate the treatment with best supportive treatment. If it fails, transanal irrigations are started. Moreover, if this fails, invasive procedures are recommended (such as sacral nerve modulation or stoma). Some authors recommend the perineal stoma as an alternative stoma formation site in patients were sphincter preservation is not possible (14). However, data on the risk of LARS in this subgroup of patients is still lacking.

## Objectives

The primary objective of this study was to evaluate if transanal irrigation improves bowel function and quality of life in patients following low anterior resection compared with best supportive care.

Specific objectives were as follows:
1.To assess the proportion of patients with transanal irrigation that reduces the symptoms of LARS (decrease in absolute score).2.To assess the proportion of patients with best supportive care that reduces the symptoms of LARS (decrease in absolute score).3.Compare results between groups.

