### Eligibility criteria

Inclusion criteria are as follows:
•Subject is an adult (≥18 years).•Agrees to participate in a study.•A low anterior resection (robotic, laparoscopic, or open) was performed [anastomosis up to 5–7 cm from the anocutaneous line when assessed with a finger or endo(recto)scope] following long-course (chemo)radiotherapy [the patients treated with 5-fluorouracil (FU) or capecitabine and radiation for 5 weeks; radiation therapy is given once a day at 1.8 Gy/day for a total of 50.0 Gy (1.8 Gy/fraction to the gross tumor and 45 Gy to pelvic lymph nodes)].•>3 months have passed since the operation or the closure of the ileostomy (if formed).•No anastomotic leak or stenosis (assessed clinically, during examination, and/or via a proctogram).•LARS >30 points (major LARS).Exclusion criteria are as follows:
•Tumor recurrence/progression.•Pregnancy.•Diagnosed with inflammatory bowel disease (ICD codes K50–59).•Side-to-end anastomosis.•Palliative care.•Will not be able to perform irrigation.

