### Sample size

A sample size of 40 is planned (an improvement of 5 points on the LARS scale):
•20 transanal irrigation group (experimental) and•20 best supportive care group (control).To demonstrate a 5-point difference (with 80% certainty) between the intervention group and the control group, 34 patients were required to participate in the study (17 in each study arm). Taking into account a drop off of 20%, at least 20 patients per group will be needed. The primary endpoint was LARS score analyzed by unpaired *t* test.

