### Outcome measures

The objectives of the trial are to evaluate in what proportion of patients (percentage) transanal irrigation and in what proportion of patients (percentage) the best supportive treatment reduces the symptoms of LARS score (change in absolute score), compare the results, and evaluate the statistical reliability. The secondary outcomes would be assessing the change in single LARS score's items.

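### The objectives compare the proportion of patients with any fall in LARS score, but the trial is sized for a 5-point difference in mean score; the proportion is inflated in both arms and has well under 80% power.

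*Protocol article*

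**What the plan says.** Three sections of the protocol article bear on the main comparison.

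- **Objectives.** Specific objective 1 is "To assess the proportion of patients with transanal irrigation that reduces the symptoms of LARS (decrease in absolute score"). Objective 2 is the same for best supportive care, and objective 3 compares the groups.
- **Outcome measures.** The proportions are repeated as the trial's objectives: in what percentage of patients each treatment "reduces the symptoms of LARS score (change in absolute score), compare the results, and evaluate the statistical reliability". The gloss is now a change rather than a decrease. Again there is no minimum and no visit, although Assessments has the scales completed every 3 months for 1 year.
- **Sample size.** The planned 40 patients are tied to "an improvement of 5 points on the LARS scale". The next sentence gives the aim of the calculation: "To demonstrate a 5-point difference (with 80% certainty) between the intervention group and the control group". Its result, before allowance for dropout, is 17 per arm or 34 in total. The section ends: "The primary endpoint was LARS score analyzed by unpaired" t test.

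Eligibility criteria require "LARS >30 points (major LARS"). No SD, significance level, test-retest error or smallest important individual change is stated.

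**The concern.** The Objectives and Outcome measures sections ask for a comparison of two proportions. The Sample size section powers a comparison of two means. These are different endpoints with different power at the same sample size, and the text does not say which one carries the 80%.

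The proportion is also a weak one. Read literally, a 1-point fall is a response. Patients are admitted because their score was above 30 on one occasion, so on re-measurement the average tends to drift down without any treatment effect. The Introduction adds that symptoms may improve with time after surgery in some patients, and entry is allowed from just over 3 months. High percentages can therefore be expected in both arms. They could be read as treatment success, and the room for a difference between arms shrinks.

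**Working it through.** **1. The plan's own figure.** Inputs from Sample size: difference 5, power 80%, 17 per arm, unpaired t test. SD and alpha are not given, so 17 cannot be checked independently; two-sided 0.05 is assumed and the SD is back-solved.

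- Normal approximation: SD = 5 × √(17/2) / (1.960 + 0.842) = 14.58 / 2.802 = 5.20.
- Exact t test: SD = 5.05.

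The figure is thus consistent with an SD of about 5.05 for the quantity tested. Below, this is taken as the SD of the change in score.

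**2. Patients with no true change.** Assumed model: true score T ~ N(mean, true SD); baseline and follow-up are each T plus independent error, rounded to whole points and limited to 0–42 (an assumed range). Only patients with a baseline above 30 are kept. The means refer to the population before that selection. Assumed ranges: true mean 28–36, true SD 4–9, error SD 3–4.

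| Scenario (true mean, true SD, error SD) | Any fall | Fall of 5 or more |
|---|---|---|
| 28, 4, 4 (highest) | 69% | 39% |
| 33, 6, 4 | 52% | 24% |
| 36, 9, 3 (lowest) | 36% | 11% |

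Over the whole grid, any fall occurs in about 36–70% and a fall of 5 or more in 11–39%. The mean score fell in every scenario. Unchanged scores pull the share down; selection on a high baseline pushes it up.

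**3. Power of the proportion if the planned effect is true.** Let controls improve by m points on average and the irrigation arm by m + 5, with SD of change 5.05. For whole-point scores:

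- P(any fall) = Φ((mean improvement − 0.5) / 5.05)
- P(fall of 5 or more) = Φ((mean improvement − 4.5) / 5.05)

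For example, with m = 2, any fall is Φ(1.5/5.05) = 62% v Φ(6.5/5.05) = 90%. Power is the exact probability that a two-sided Fisher test gives p ≤ 0.05 with 17 per arm.

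| m | Any fall, control v irrigation | Power, any fall | Power, fall of 5 or more |
|---|---|---|---|
| −1 | 38% v 76% | 49% | 40% |
| 0 | 46% v 81% | 45% | 45% |
| 1 | 54% v 86% | 40% | 49% |
| 2 | 62% v 90% | 36% | 50% |
| 3 | 69% v 93% | 30% | 49% |
| 4 | 76% v 95% | 22% | 45% |
| 5 | 81% v 97% | 13% | 40% |

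The t test has 80% in every row, by construction.

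**4. Cross-check with a less conservative test.** With SD 5.2, m = 0 and no rounding, the proportions are 50% v Φ(5/5.2) = 83%. The normal approximation gives about 54% power at 17 per arm. For 80% power, n = [1.960√(2 × 0.666 × 0.334) + 0.842√(0.5 × 0.5 + 0.832 × 0.168)]² / 0.332² = 1.833² / 0.110 ≈ 31 per arm, against the 20 planned.

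**The case against.** Four objections deserve an answer.

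- **The primary analysis is already stated.** Sample size does name the LARS score with a t test as the primary endpoint, so the power loss concerns an analysis the trial was not sized for. That is true, but Objectives and Outcome measures put the proportions first, and the latter leaves only change in single LARS items as secondary. The sections need reconciling.
- **The comparison is fair.** A reader might infer that regression to the mean biases the result. It does not: allocation is random with equal probability, so the drift acts on both arms. Nor does the protocol claim that one arm's percentage proves efficacy, since objective 3 plans the comparison. What remains is that objectives 1 and 2 describe each arm's percentage as what the treatment reduces, which invites that reading.
- **Five points is not an individual cut-off.** A reader might infer that the responder rule should have been 5 points because the trial was sized on 5. The parenthetical about an improvement of 5 points is loose, but the calculation uses a difference between group means. The documents give no support for 5 points as a meaningful change in one patient. The mismatch is first one of endpoint type.
- **A 5-point cut is not reliably better.** At m = 0 the two cut-offs have equal power, and if controls worsen by 1 point, any fall does better. The advantage appears only when controls improve. This objection stands.

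**Conclusion.** The concern holds as a conflict between sections with a measurable cost. The objectives compare proportions with any fall; the sample size supports a comparison of mean scores. If the planned 5-point effect is true, the proportion has about 45% power when controls do not change, and 36% down to 13% when they improve by 2 to 5 points, against 80% for the t test. A 5-point cut gives about 40–50% over controls improving by 0 to 5 points, so no change of cut-off considered here repairs the power at this size.

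The power figures rest on two-sided 0.05, the back-solved SD applied to change, normal changes and Fisher's test. The 36–70% share of unchanged patients counted as improved rests on assumed distributions and moves mainly with the assumed true mean and spread. It would be tempting to say that half of unchanged patients will be labelled improved; that lies within the range, but the documents give no error, spread or frequency of unchanged scores from which to establish it. Likewise, it is not shown that the response percentage in the irrigation arm would be mostly noise.

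**What to change.** In Objectives and Outcome measures, state that the between-arm comparison of LARS score described under Sample size is primary and is the analysis that carries the 80% power. Keep the responder proportion as a secondary outcome with:

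- a minimum fall above measurement noise and one named visit, both fixed before the analysts are unblinded. At least 5 points at 12 months is one option; it should be described as a chosen cut-off, because the 5 points under Sample size is a mean difference;
- a between-arm risk difference with 95% confidence interval as the reported result;
- within-arm percentages given as description only, not as treatment effects.

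If the proportion is meant to be primary, the trial has to be re-sized for it. State the SD and alpha behind the 17 per arm in either case.

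The change is mainly wording, with two costs. Reported response percentages will be lower in both arms. Trial status also records 24 patients included by January 2024, so this is a change to an outcome definition during the trial; it must be dated, documented and justified without reference to results by arm.

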## Methods and analysis

### Study design

This is a multicenter randomized clinical trial. Centers from Lithuania (four centers), UK (at least one center), Denmark (at least one center), and other countries will be invited to participate through the European Society of Coloproctology’s (ESCP) trial map.

The main objective of this clinical trial is to evaluate whether transanal irrigation improves bowel function and quality of life in patients following low anterior resection best supportive care. This will be accomplished by recording the patient's complaints (defecation, urination problems, deterioration of quality of life) after the operation, filling the LARS score (3, 15), Wexner score (16), and quality of life questionnaires [European Organization for Research and Treatment of Cancer (EORTC) CR29 (17) and Measure Yourself Medical Outcomes Profile (MYMOP)] (18) with additional questions: Would you advice this treatment to anybody else? Did your quality of live improve? Did the bowel function improve? Are you satisfied with the treatment? Did you expect the treatment would help? These questions will be rated from 0 to 5. All will be filled in again during the visit every 3 months for 1 year.

### Study population

All patients who developed LARS and met the inclusion criteria will be offered participation in this clinical trial.

### Eligibility criteria

Inclusion criteria are as follows:
•Subject is an adult (≥18 years).•Agrees to participate in a study.•A low anterior resection (robotic, laparoscopic, or open) was performed [anastomosis up to 5–7 cm from the anocutaneous line when assessed with a finger or endo(recto)scope] following long-course (chemo)radiotherapy [the patients treated with 5-fluorouracil (FU) or capecitabine and radiation for 5 weeks; radiation therapy is given once a day at 1.8 Gy/day for a total of 50.0 Gy (1.8 Gy/fraction to the gross tumor and 45 Gy to pelvic lymph nodes)].•>3 months have passed since the operation or the closure of the ileostomy (if formed).•No anastomotic leak or stenosis (assessed clinically, during examination, and/or via a proctogram).•LARS >30 points (major LARS).Exclusion criteria are as follows:
•Tumor recurrence/progression.•Pregnancy.•Diagnosed with inflammatory bowel disease (ICD codes K50–59).•Side-to-end anastomosis.•Palliative care.•Will not be able to perform irrigation.

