### Statistical analysis

For statistical analysis, we will use the intention to treat principle.

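### The primary unpaired t test makes no allowance for time since surgery, which entry leaves open above 3 months and the protocol itself links to recovery

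*Protocol article*

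**What the plan says.** Under Eligibility criteria, the time condition is a floor only: ">3 months have passed since the operation or the closure of the ileostomy (if formed"). Neither the inclusion nor the exclusion list sets a ceiling. The other relevant entry condition is severity: "LARS >30 points (major LARS").

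The Introduction treats time since surgery as relevant to outcome. Of an earlier 27-patient study of irrigation it remarks: "However, this study included patients with chronic LARS as well as patients with early symptoms following the surgery". It then explains that some patients' "symptoms may improve over the time following the operation, while others can suffer from colonic dysfunction and nerve damage", and says that these problems do not appear to change with time. It also reports that "50% of patients have these symptoms 5 or more years after the surgery". A patient a little over 3 months from ileostomy closure and one several years from surgery can therefore both be eligible.

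Under Sample size: "The primary endpoint was LARS score analyzed by unpaired" t test. The Statistical analysis section adds only: "For statistical analysis, we will use the intention to treat principle". That settles who is analysed and in which arm, not what the model adjusts for. The Randomization section describes equal allocation by computer-generated numbers and sealed envelopes and names no stratification factor. The list of baseline data under Data collection does not include time since surgery or stoma closure.

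**The concern.** The protocol names a factor that may drive change in the LARS score whatever the treatment, admits patients across its whole range above 3 months, and then fixes a primary test that cannot use it. This is not a complaint about detail left to an analysis plan. The article states the test, and an unpaired t test has no covariate.

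Precision is at stake. If recently operated patients recover more on their own during the year of follow-up, that difference becomes residual variance in an unadjusted comparison. With 20 patients per arm, the share of recently operated patients can also differ between arms by chance, and the t test has no means of correcting for it.

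**Working it through.** **Inputs from the protocol article (Sample size).** Target difference 5 LARS points; 80% power; 17 per arm; 20 per arm planned after allowance for dropout; unpaired t test.

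**Inputs not in the documents, so assumed.** Two-sided alpha of 0.05; the SD; the share p of early patients; and g, the extra natural recovery of early over chronic patients in LARS points. No recovery figure appears anywhere, and early is not defined. I take p = 0.5 and g = 4 to 8 purely as illustration.

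**Step 1. The plan's own figure.** No SD is stated, so 17 per arm cannot be reproduced forwards, only solved backwards. With the noncentral t distribution, 17 per arm and 80% power need a standardised difference of 0.991, so SD = 5 / 0.991 = 5.05. The normal approximation gives 5.20. If the test were one-sided at 0.05, the SD would be about 5.74 (t) or 5.86 (normal). I use 5.05.

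**Step 2. SD when early and chronic patients are mixed.** This treats 5.05 as the SD within each time group: SD_total = sqrt(5.05² + p(1 − p)g²).
- g = 4: sqrt(25.50 + 0.25 × 16) = sqrt(29.50) = 5.43
- g = 8: sqrt(25.50 + 0.25 × 64) = sqrt(41.50) = 6.44

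**Step 3. Power of the unadjusted t test for 5 points.**

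| g | SD | 17 per arm | 20 per arm |
|---|---|---|---|
| 0 | 5.05 | 80% | 86% |
| 4 | 5.43 | 74% | 81% |
| 8 | 6.44 | 59% | 67% |

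The 17-per-arm column applies only if dropout reduces the arms to that size.

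**Step 4. Chance imbalance.** With 20 per arm and p = 0.5, the SD of the between-arm difference in early share is sqrt(0.25 × 2/20) = 0.158, or 16 percentage points. The matching 1-SD shift in the estimate is 0.158 × 4 = 0.63 to 0.158 × 8 = 1.26 points. The chance of an imbalance of at least 20 percentage points is about 27% (23% if p = 0.3).

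This is not a second loss on top of Step 3. At 20 per arm the standard error without mixing is 5.05 × sqrt(2/20) = 1.597. Adding the imbalance variance for g = 4 gives sqrt(1.597² + 0.632²) = 1.718, which is exactly 5.43 × sqrt(2/20). The inflated SD already contains the imbalance.

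**Step 5. Error rate and the gain from adjustment.** Simulation with 20,000 runs, 17 per arm, p = 0.5 and SD 5.05:
- Type I error was about 5% for both the t test and the adjusted model at every g from 0 to 10.
- At g = 5, power was 71% unadjusted and 78% adjusted for early/chronic status. At g = 8 it was 59% and 79%.
- At g = 0, adjustment cost about one point of power (80% against 79%).

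The simulated model used the correct two-group term. A continuous term such as log months recovers this only as far as its shape fits the true pattern.

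**The case against.** The strongest reply is that nothing here threatens validity. The control arm is concurrent and allocation is random, so natural recovery occurs in both arms and balances in expectation. This stands. A reader might infer that open-ended entry biases the irrigation effect; the design does not support that, and the simulated error rate stays near 5%.

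A reader might also infer that the trial repeats the flaw it finds in the earlier study. The documents cannot show this. They give no entry window for that study and do not define early symptoms, while this trial excludes the first 3 months and everyone at or below 30 LARS points. The early/chronic remark is a background comment. The stated objectives do not include separating the two, and the limitations of earlier trials that the article lists as main ones are dropout, small numbers and short follow-up.

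Thirdly, the power figures rest on assumptions. If the unstated planning SD came from an already mixed population, the loss is inside the 17 per arm and power does not fall below 80% on this account. That also stands: neither reading can be checked.

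Finally, covariates and strata are often left to a full protocol or analysis plan. That would answer a complaint about silence, but the article names an unadjusted test. The reply lowers the weight of the point without removing it.

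**Conclusion.** The point holds as a matter of precision and prespecification. Entry has a floor and no ceiling, the protocol itself says that recovery with time differs between patients, and the stated primary test cannot take that into account. In 40 patients, this forgoes precision and leaves chance imbalance in time since surgery uncorrected.

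Its size is unknown from the documents. The 74% to 59% at 17 per arm, or 81% to 67% at 20 per arm, require all of the following: two-sided 0.05, an SD of 5.05 that applies within a time group, half the patients early, and a 4 to 8 point recovery difference. It would be wrong to read these figures as showing that the trial is underpowered. If the SD already includes the mix, adjustment would only gain precision over what was planned. The amendment is worth making because it is cheap, not because a large loss has been shown.

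**What to change.** Leave eligibility as it is. Record months since operation or ileostomy closure for every patient. The value is needed to apply the entry criterion, so it should be retrievable for the 24 patients already included by January 2024.

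Before outcomes are analysed, replace the unpaired t test with an ANCOVA of the LARS score on treatment, baseline LARS and log months since operation or closure. Baseline LARS is already obtained to establish major LARS at entry. The timing matters, because a covariate added after outcomes have been seen would look data-driven.

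Any split of results by time since surgery should be descriptive only. The documents offer no cut-point, and an even split would leave about 10 patients per arm in each half (20 / 2).

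The cost is one additional recorded value and two degrees of freedom in the primary model, one for each covariate.
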